#### Sample Size Considerations

2.7.2

We estimate that 35% of patients will die during the initial hospital course (0 days alive out of hospital) [31]. For patients surviving hospitalization, the expected mean number of days out of hospital will be 15 days; the mean number of days outside hospital will therefore be 9.8 days for the population, with an estimated standard deviation of 7 days. To detect an increase of 1.5 hospital free days with power > 90% and a two‐sided significance level of 5%, a total of 920 patients will be required.

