## Introduction

1

In Europe, the incidence of Out‐of‐Hospital Cardiac Arrest (OHCA) is approximately 55 per 100.000 inhabitants, and in Denmark more than 5.000 individuals suffer from OHCA yearly, with most cases having a presumed cardiac etiology. Improved prehospital logistics and bystander‐performed basic life support have considerably improved the outcome over the last decades. However, the 30‐day mortality rate remains above 80% [1]. For unconscious patients with OHCA who are resuscitated successfully and admitted to an intensive care unit (ICU), the 30‐day mortality remains at approximately 50% with the main cause of death being irreversible brain injury [2].

Intensive care following resuscitation from OHCA is based on a set of interventions aimed at circulatory stabilization and mitigation of anoxic brain injury [3, 4]. Patients frequently experience postcardiac arrest syndrome and persistence of the condition that precipitated the cardiac arrest [5]. These patients are often admitted to hospital in an unstable condition necessitating both circulatory and respiratory support.

With the nationwide DANOHCA trial we seek to evaluate four new potential interventions for improving outcomes after OHCA. A separate protocol manuscript will be published for each intervention, with the present manuscript describing the intervention of prophylactic olanzapine compared to placebo for reducing delirium incidence and shortening hospitalization (LINK; Dexamethasone, Wake‐up call, Backrest).

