### Strengths

3.1

The trial has several strengths. It is a nationwide, investigator‐initiated, multicenter trial testing commonly used treatments, all with conflicting or limited evidence. The trial has a pragmatic design making it feasible and easy to embed in routine clinical practice. Automated randomization and blinding of the olanzapine versus placebo intervention to both the clinical personnel, site investigators, and statisticians minimizes the risk of bias. The risk of side effects and complications is likely to be limited, as olanzapine is a well‐known drug given within normal dosage regimens for a short period of time. The use of a validated diagnostic tool for the assessment of delirium may increase the generalizability of the results. In the event of delirium, the trial design allows for treatment according to local practices at the enrolling site, ensuring appropriate care for patients who develop delirium.

Finally, the assumptions regarding outcomes after cardiac arrest are likely to be realistic, as the sample size is based on previous data from our department [31]. With 920 participants, the trial provides more than 90% power to detect a 1.5‐day difference in days alive and out of the hospital at 30 days. This is a clinically meaningful and patient‐centered outcome.

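### The planning SD of 7 days is below the minimum that the plan's own assumptions allow (7.15), so the stated power of more than 90% for 1.5 days with 920 patients is not supported

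*Protocol article*

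**What the plan says.** The sample-size argument is in section 2.7.2 of the protocol article (Sample Size Considerations).

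- Zeros: "We estimate that 35% of patients will die during the initial hospital course (0 days alive out of hospital").
- Survivors: "the expected mean number of days out of hospital will be 15 days".
- Population: "the mean number of days outside hospital will therefore be 9.8 days for the population, with an estimated standard deviation of 7 days".
- Target: "To detect an increase of 1.5 hospital free days with power > 90" per cent, at a two-sided 5% level.
- Result: "a total of 920 patients will be required".

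Section 3.1 (Strengths) repeats the claim: "With 920 participants, the trial provides more than 90% power to detect" a difference of 1.5 days. The Conclusion cites the large sample among its reasons for expecting a conclusive answer. The Abstract and sections 2.11.3 and 2.12 give the enrolment target as 1000. Section 2.7.3 makes the Wilcoxon rank-sum test the primary analysis and adds the mean difference with a 95% confidence interval as a supplementary analysis.

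**The concern.** The population mean of 9.8 days is derived from a two-part mixture: 35% at zero and 65% averaging 15. The same mixture fixes a lower bound for the population SD, because patients at zero and patients around 15 differ from each other whatever happens within the survivors. The stated SD lies below that bound. The calculation has almost no slack, so even a small increase in the SD takes the power under 90%, and realistic variation in survivors' length of stay is not a small increase.

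What is at stake is the reading of a neutral result. If the article says that the trial had more than 90% power for 1.5 days, readers will treat a neutral result as stronger evidence against such a benefit than the design can give.

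**Working it through.** **Inputs.** From section 2.7.2: proportion at zero 0.35, survivor mean 15 days, SD 7, difference 1.5 days, two-sided 5%, N = 920. From the Abstract and sections 2.3 and 2.12: 1:1 allocation and 1000 patients planned. The survivor SD, called s below, is not in the documents.

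**Step 1: reproduce the plan's figure.** With a common SD, n per arm = 2 × (1.960 + 1.282)² × 7² / 1.5² = 458, or 916 in total, against 920 stated. Power with 460 per arm is 90.1%. The 920 is therefore the two-mean formula with SD 7.

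**Step 2: the SD implied by the inputs.** The mean is 0.65 × 15 = 9.75, matching the stated 9.8. The variance is

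0.65 × s² + 0.65 × 0.35 × 15² = 0.65 × s² + 51.19.

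At s = 0, with every survivor at exactly 15 days, the SD is √51.19 = 7.15. (If the mean is taken as exactly 9.8, the floor is 7.14.) A population SD of 7 cannot occur.

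**Step 3: the slack.** The largest SD that keeps 90% power for 1.5 days is 1.5 / [(1.960 + 1.282) × √(2/n)].

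- With n = 460 per arm this is 7.02, already under the floor.
- With n = 500 per arm it is 7.32, which requires s ≤ √[(7.32² − 51.19)/0.65], about 1.9 days.

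**Step 4: power in the same calculation.** Every row with s above 0 uses an assumed survivor SD.

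| s (days) | Population SD | Power, 920 | Power, 1000 | N for 90% |
|---|---|---|---|---|
| 0 (floor) | 7.15 | 88.9% | 91.2% | 958 |
| 3 | 7.55 | 85.4% | 88.1% | 1066 |
| 5 | 8.21 | 79.1% | 82.3% | 1260 |
| 7 | 9.11 | 70.4% | 74.0% | 1552 |
| 8 | 9.63 | 65.6% | 69.2% | 1734 |

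The difference detectable with 90% power at 1000 patients is (1.960 + 1.282) × SD × √(2/500) = 0.205 × SD. That is 1.7 days at SD 8.21, 1.9 at 9.11 and 2.0 at 9.63.

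**Step 5: the planned test.** Wilcoxon power was simulated for 1000 patients (2000 runs; survivors' days drawn from a scaled beta distribution on 0 to 30, rounded to whole days). Each scenario adds 1.5 days to the mean in a different way.

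| s (days) | Stay only (survivor mean 15 + 1.5/0.65 = 17.3) | Mortality only (35% to 25%) |
|---|---|---|
| 3 | 99.9% | 79.8% |
| 5 | 85.6% | 79.1% |
| 7 | 59.1% | 79.7% |
| 8 | 49.9% | 79.3% |

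The same 1.5 days gives very different Wilcoxon power depending on the survivor spread and on where the gain arises.

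**The case against.** The strongest reply is that the strict contradiction is thin: 7 against 7.15, where 7.15 itself rounds to 7 and the plan calls its SD an estimate. That is true, but it does not rescue the claim. To round to 7 the population SD must be below 7.5, which needs a survivor SD under about 2.8 days on a 0 to 30 scale. Even then, power at 920 is below 90% in the plan's own calculation.

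The 88.9% ceiling also takes the same SD in both arms, as the plan's formula does. If the whole gain came from mortality falling from 35% to 25%, the variance in the active arm would be 0.75 × 0.25 × 15² + 0.75 × s² = 42.19 + 0.75 × s². The average over the arms would then be 46.69 + 0.70 × s². Staying within 7.02² = 49.3 again needs s below about 1.9 days, so the conclusion is unchanged.

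Some stronger readings are tempting, and the documents do not support them.

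- **That the real power is 65% to 80%.** This needs an assumed survivor SD of 5 to 8 days and a comparison of means. The documents fix only the ceiling, and Wilcoxon power can lie on either side of that range.
- **That the 7 is the survivors' SD, misapplied.** This is conjecture. Section 3.1 attributes the sample-size assumptions to departmental data that are not shown.
- **That nothing is allowed for exclusions from the modified intention-to-treat set.** Enrolment of 1000 exceeds 920 by 80 patients, and section 2.7.5 expects under 5% missing primary outcome data.
- **That the Introduction contradicts the 35%.** Its statement that "mortality remains at approximately 50% with the main cause of death being irreversible brain injury" concerns unconscious resuscitated patients admitted to intensive care in general. The trial's exclusions select a different population.

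It is also fair to say that a neutral result should be read from its confidence interval, which section 2.7.3 provides. That limits the harm but does not make the published power figure correct.

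**Conclusion.** Wrong as written. Without any outside assumption, the SD of 7 is incompatible with the plan's own zeros and survivor mean. In the calculation that produces 920, power for 1.5 days is at most 88.9% with 920 patients and 91.2% with 1000. That ceiling requires no spread at all among survivors, and 90% at 1000 requires a survivor SD of about 1.9 days or less.

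The larger shortfall is conditional. For an assumed survivor SD of 5 to 8 days, power is about 79% to 66% at 920 and 82% to 69% at 1000, and 1000 patients give 90% power for about 1.7 to 2.0 days. These are two-mean figures and should not be quoted as the power of the Wilcoxon test, which the documents do not allow anyone to state as a single number.

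**What to change.** Keep the enrolment target and the primary test.

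1. In 2.7.2, replace the SD of 7 with a population SD that includes both the zeros and the spread among survivors, and give its source. The pooled SD from patients already enrolled, computed without reference to allocation, would serve.
2. Recompute power for the Wilcoxon test under stated scenarios: gain through shorter stay, through lower mortality, and through both.
3. Restate the power in 2.7.2 and 3.1 with these assumptions beside it, preferably before the last patient is included (expected July 2026 according to section 2.12).
4. Bring the Conclusion's expectation of a conclusive answer into line with the restated figure.

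The cost is a blinded calculation and changes of wording, with no extra patients and no change to the analysis. The downside is that the stated power becomes less favourable.

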#### Analysis of Primary Outcome

2.7.3

Days alive outside the hospital within 30 days will be analyzed using the Wilcoxon rank‐sum test between the two treatment arms. Results will be presented as medians with interquartile ranges and 95% confidence intervals for the median difference (calculated using nonparametric bootstrapping with 1000 resamples). Relative differences between days alive outside hospital groups will be reported as percentages, with confidence intervals obtained by bootstrapping. As a prespecified supplementary analysis, days alive outside the hospital within 30 days will also be expressed as the mean between‐group difference with a 95% confidence interval. Sensitivity analyses using mixed‐effects linear regression models with site as a random effect, adjusting for other interventions, will be performed to assess the robustness of the findings.

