#### Analysis of Survival Data (Secondary Outcome)

2.7.4

We will use log‐binomial regression to estimate the relative risk of 90‐day mortality, defined as the proportion of patients who die from any cause between randomization and Day 90. If log‐binomial models are infeasible due to nonconvergence, logistic regression models will be used instead, and odds ratios will be reported instead of relative risk. As additional analyses, Kaplan–Meier curves for each allocation group will be estimated, graphically displayed, and compared by the log‐rank test. Furthermore, Cox proportional hazard models will be applied to estimate hazard ratios with 95% confidence intervals for time to death between treatment groups. As prespecified subgroup analyses, the interaction between treatment allocation and each of the following baseline variables will be assessed: sex, age, time to ROSC, lactate level upon hospital admission, shockable primary rhythm, witnessed cardiac arrest, bystander‐performed cardiopulmonary resuscitation, and presence of STEMI consistent with acute myocardial infarction. Proportional hazards assumptions will be assessed using Schoenfeld residuals and log–log plots. If deviations from the proportional hazards assumption are detected, the relevant covariates will be included with time‐varying HR instead, or if this is not sufficient to solve the deviation, Cox regressions with stratified baseline hazards will be utilized. Further, causes of death (cardiovascular, neurological, multiorgan failure) between the treatment arms will be compared as competing risks with the Nelson–Aalen cumulative incidence method as hypothesis generating. Any changes from the prespecified analysis plan will be reported.

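### The primary Wilcoxon test and its sensitivity model use none of the prognostic baseline variables the article lists; adjusting for them would add power at no cost in patients

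*Protocol article*

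**What the plan says.** Under Analysis of Primary Outcome the article fixes the test: "Days alive outside the hospital within 30 days will be analyzed using the Wilcoxon" rank-sum test, comparing two arms with no covariates. The abstract names the same test. A mean between-group difference is supplementary. The sensitivity analysis is a mixed linear model with site as a random effect, "adjusting for other interventions, will be performed to assess the robustness of the findings". General Principles adds that every regression is adjusted for site. No prognostic variable is named in any of these places.

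Such variables are listed under Analysis of Survival Data, for interaction tests within the mortality analysis: "sex, age, time to ROSC, lactate level upon hospital admission, shockable primary rhythm, witnessed cardiac arrest", followed by bystander CPR and STEMI. Collection of these variables is therefore planned.

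Sample Size Considerations supplies the outcome model: "We estimate that 35% of patients will die during the initial hospital course (0 days alive out of hospital"); among survivors "the expected mean number of days out of hospital will be 15 days"; and a population mean of 9.8 days "with an estimated standard deviation of 7 days". The stated requirement is 920 patients; 1000 are planned.

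**The concern.** Patients who die in hospital score 0 days, so baseline variables that predict death should also predict this outcome. Leaving them out of the primary test puts explainable variation into the error term. Randomisation is not stratified by site, and the article describes no stratification by prognosis, so the design does not supply the balance that adjustment would.

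What is at stake is precision. A wider interval and lower power make a true effect of the planned size easier to miss. The article gives last inclusion as July 2026 at a fixed total of 1000, so the analysis model is one of the few places where precision can still be gained without recruiting anyone.

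**Working it through.** **Inputs from the article.** Difference 1.5 days; two-sided alpha 5%; SD 7; 35% at 0 days; survivor mean 15; 1:1 allocation; N = 920 required, 1000 planned.

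**Inputs assumed.** Survivor SD s = 5, 7 or 9 days. R², the share of outcome variance explained by baseline variables, = 0.10, 0.20 or 0.30. The documents give neither.

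**1. The plan's own figure.** The two-sample normal formula with difference 1.5, SD 7 and 90% power gives 458 per arm, 916 in total, against 920 stated. Power at 920 is 90.1%. The figure reproduces.

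**2. How much of the variance comes from death.** For a mixture with 35% at zero and a survivor mean of 15:

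Variance = 0.65 × s² + 0.35 × 0.65 × 15² = 0.65 × s² + 51.2

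- s = 5: 16.25 + 51.2 = 67.4, SD 8.21, share due to death 51.2/67.4 = 76%
- s = 7: 31.85 + 51.2 = 83.0, SD 9.11, share 62%
- s = 9: 52.65 + 51.2 = 103.8, SD 10.19, share 49%

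With s = 0 the SD is still 15 × √(0.35 × 0.65) = 7.15, so the planned SD of 7 does not fit the plan's other inputs. That is a separate sample-size point; it is used here only to choose a realistic SD.

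**3. Effect of adjustment.** The residual SD is SD × √(1 − R²). Power = Φ(1.5 / (residual SD × √(2/n)) − 1.96), with n per arm. Worked case, N = 1000, s = 7, R² = 0: 9.11 × √(2/500) = 0.576; 1.5/0.576 = 2.60; Φ(0.64) = 74.0%.

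| N | s | Unadjusted | R² 0.10 | R² 0.20 | R² 0.30 | Gain (points) |
|---|---|---|---|---|---|---|
| 920 | 5 | 79.1% | 83.1% | 87.2% | 91.2% | 4.0 to 12.1 |
| 920 | 7 | 70.4% | 74.9% | 79.7% | 84.7% | 4.5 to 14.3 |
| 920 | 9 | 60.7% | 65.3% | 70.4% | 76.1% | 4.6 to 15.4 |
| 1000 | 5 | 82.3% | 86.1% | 89.8% | 93.2% | 3.8 to 10.9 |
| 1000 | 7 | 74.0% | 78.3% | 82.9% | 87.5% | 4.3 to 13.5 |
| 1000 | 9 | 64.3% | 68.9% | 74.0% | 79.4% | 4.6 to 15.1 |

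At R² = 0.20 the gain equals 1/(1 − 0.20) = 1.25, that is, 25% more patients. At the stated SD of 7 and N = 920, R² = 0.20 moves power only from 90.1% to 95.3%.

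**4. Check on the rank scale.** Step 3 is for a difference in means. A simulation of a zero-inflated outcome (N = 920, 1,500 runs per scenario, realised difference 1.40 to 1.47 days, benefit on both survival and survivors' days) compared Wilcoxon with rank ANCOVA on one prognostic score:

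- s = 5: 78.9% to 82.6% at R² 0.12; 78.9% to 87.5% at R² 0.25; 76.0% to 92.0% at R² 0.38
- s = 7: 67.7% to 71.1% at R² 0.11; 64.8% to 75.3% at R² 0.24; 63.6% to 81.9% at R² 0.36
- R² near 0: 80.9% and 80.5% (s = 5); 65.6% and 65.1% (s = 7)

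The gain is of the same order as in step 3, and adjusting for a useless score costs almost nothing.

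**The case against.** The strongest reply is that nothing here is an error. In a randomised trial the unadjusted Wilcoxon is valid, its type I error already allows for chance imbalance, and with about 500 per arm large imbalances are unlikely. That stands. A reader might infer that the primary result would be biased, and the documents do not support that reading.

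The separate SAP is not shown and may already contain an analysis adjusted for prognosis, so it cannot be said that these variables are used nowhere else. That also stands. The Wilcoxon as primary test, and the terms named for the sensitivity model, are nevertheless stated choices in this article.

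A reader might also put the loss at a fixed 10 points. No document figure supports this. It requires R² of about 0.21 to 0.26 with a total SD of 8 to 10 at N = 920 (about 0.21 to 0.30 at N = 1000). The article lists the variables for interaction tests and does not say how strongly they predict the outcome. Comparing an unadjusted rank test with an adjusted mean difference would overstate the gain, because test and covariates then change together; the simulation above stays on the rank scale.

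Finally, changing the primary test is late. Recruitment began in June 2023, the 500-patient safety review has been held, and General Principles describes the SAP as published alongside the protocol articles. This is a real cost. Against it, the statisticians are blinded to olanzapine allocation, the interim review had no formal efficacy or futility testing, and the Publication Plan allows the SAP to appear up to the last inclusion.

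**Conclusion.** The point holds as a recommendation on efficiency. The primary test and its sensitivity model, as the article states them, use no prognostic baseline variable although several are listed. Adjustment would add roughly 4 to 15 percentage points of power for R² between 0.10 and 0.30 and survivor SD between 5 and 9 days. Both ranges are assumptions. That death accounts for about half to three quarters of the variance follows from the plan's inputs together with the assumed survivor SD. That the listed variables predict death is a reasonable expectation which the documents do not quantify.

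It would be tempting to conclude that adjustment makes good the power shortfall caused by the planned SD of 7. It generally does not: among the combinations tabulated, power passes 90% only at survivor SD 5 with R² 0.30. The SD and power statement needs its own correction.

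**What to change.** Before unblinding, and in a dated amendment, prespecify one covariate-adjusted rank-based primary test. Rank ANCOVA stays closest to the stated Wilcoxon; a proportional odds model is an alternative. Name one, not both. Covariates: age, time to ROSC, shockable rhythm, lactate, witnessed arrest, bystander CPR, site and the three other allocations. Keep the unadjusted Wilcoxon as the supporting analysis, and align the abstract, Analysis of Primary Outcome and the SAP.

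If the sponsor prefers not to change the named primary test at this stage, the minimum is to add the same covariates to the mixed-model sensitivity analysis already planned.

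Cost: no patients and no new data items. It needs a simple imputation rule for missing baseline values (lactate and time to ROSC, for example), set without knowledge of allocation, and an open statement that the primary test was changed late and while blinded. The SAP serves all four interventions, so its wording has to be checked for the others too. Correct the SD and power statement under Sample Size Considerations separately.

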#### Analysis of Survival Data (Secondary Outcome)

2.7.4

We will use log‐binomial regression to estimate the relative risk of 90‐day mortality, defined as the proportion of patients who die from any cause between randomization and Day 90. If log‐binomial models are infeasible due to nonconvergence, logistic regression models will be used instead, and odds ratios will be reported instead of relative risk. As additional analyses, Kaplan–Meier curves for each allocation group will be estimated, graphically displayed, and compared by the log‐rank test. Furthermore, Cox proportional hazard models will be applied to estimate hazard ratios with 95% confidence intervals for time to death between treatment groups. As prespecified subgroup analyses, the interaction between treatment allocation and each of the following baseline variables will be assessed: sex, age, time to ROSC, lactate level upon hospital admission, shockable primary rhythm, witnessed cardiac arrest, bystander‐performed cardiopulmonary resuscitation, and presence of STEMI consistent with acute myocardial infarction. Proportional hazards assumptions will be assessed using Schoenfeld residuals and log–log plots. If deviations from the proportional hazards assumption are detected, the relevant covariates will be included with time‐varying HR instead, or if this is not sufficient to solve the deviation, Cox regressions with stratified baseline hazards will be utilized. Further, causes of death (cardiovascular, neurological, multiorgan failure) between the treatment arms will be compared as competing risks with the Nelson–Aalen cumulative incidence method as hypothesis generating. Any changes from the prespecified analysis plan will be reported.

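### Mortality analysis (section 2.7.4): the estimator named for deaths by cause does not estimate cumulative incidence, and the nonconvergence rule changes the effect measure from relative risk to odds ratio

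*Protocol article*

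**What the plan says.** Both statements stand in section 2.7.4, Analysis of Survival Data, of the protocol article.

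- **Deaths by cause.** The article says that "causes of death (cardiovascular, neurological, multiorgan failure) between the treatment arms will be compared as competing risks". The method named is Nelson–Aalen, described as a "cumulative incidence method as hypothesis generating".
- **90-day mortality.** This is the first-listed secondary outcome. The planned model is log-binomial "regression to estimate the relative risk of 90‐day mortality", where the event is to "die from any cause between randomization and Day 90". If that model does not converge, "logistic regression models will be used instead, and odds ratios will be reported instead of relative risk".

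The same section also plans Kaplan–Meier curves, a log-rank test, Cox models and treatment-by-baseline interactions. Section 2.7.1 adds site as a covariate in all regressions.

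**The concern.** **Deaths by cause.** The sentence joins an estimator to a quantity that it does not estimate. Nelson–Aalen applied to one cause gives the cumulative cause-specific hazard. This is not a probability: it exceeds the incidence, and the gap grows with total mortality. An analyst who follows the named estimator and one who follows the named quantity would draw different curves from the same data. Because death is common in this population, the difference would be visible.

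**90-day mortality.** The measure of effect should follow from the question, not from whether an iterative fit succeeds. When the event is common, the odds ratio lies clearly further from 1 than the relative risk. A reader who takes it for a relative risk would see too large an effect, whether benefit or harm. If some models in a report converge and others do not, the report would mix two scales.

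**Working it through.** The article gives no numerical result for this section, so there is no figure to reproduce.

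**Inputs**

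- Total mortality F: the article gives no 90-day figure, so 35% to 50% is an assumed range. The lower end is the planning value for in-hospital death in section 2.7.2 ("We estimate that 35% of patients will die during the initial hospital course"). The upper end is the approximate 30-day mortality that the Introduction gives for unconscious resuscitated patients admitted to an ICU.
- Split by cause: none is given. Shares of 60%, 25% and 15% are assumed for illustration. The inflation factor in step 1 does not depend on them.
- Relative risks of 0.85 and 1.10: illustrative.

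**Step 1. Cumulative hazard against cumulative incidence**

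The all-cause cumulative hazard is H = −ln(1 − F). With proportional cause-specific hazards, a cause with share s has incidence s × F (Aalen–Johansen) and cumulative hazard s × H (Nelson–Aalen). The ratio is H/F for every cause.

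| Total mortality F | H | H/F | Cause with 60% share: incidence | Same cause: Nelson–Aalen | Sum over causes: incidence | Sum: Nelson–Aalen |
|---|---|---|---|---|---|---|
| 35% | 0.431 | 1.23 | 21.0% | 25.9% | 35.0% | 43.1% |
| 50% | 0.693 | 1.39 | 30.0% | 41.6% | 50.0% | 69.3% |

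Converting each hazard to 1 − exp(−s × H) does not repair this. At 35% mortality the three causes become 22.8%, 10.2% and 6.3%, which sum to 39.2%. At 50% they become 34.0%, 15.9% and 9.9%, which sum to 59.8%. Both sums still exceed the all-cause figure.

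**Step 2. Odds ratio against relative risk**

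OR = [p1/(1 − p1)] / [p0/(1 − p0)], with p1 = RR × p0.

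- p0 = 0.35, RR 0.85: p1 = 0.2975, so OR = 0.4235/0.5385 = 0.79.
- p0 = 0.50, RR 0.85: p1 = 0.425, so OR = 0.7391/1 = 0.74.
- RR 1.10: OR = 1.16 at p0 = 0.35 and 1.22 at p0 = 0.50.

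**Step 3. How likely is the fallback?**

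- *Main model.* In an illustrative simulation (1000 patients, treatment plus five sites, assumed small site differences), the log-binomial model converged in 300 of 300 runs at 35% and at 50% mortality.
- *Interaction models.* Section 2.7.4 lists interactions with age, time to ROSC and lactate, but the article does not say which model they use. A second simulation assumed log-binomial models with treatment, site, one continuous covariate and its interaction with treatment. The truth was logistic with no treatment effect, with 200 runs per setting. A run failed if it did not converge or gave a fitted risk of 1 or more. With a covariate odds ratio of 1.35 per SD, about 1–2% of runs failed at 35% mortality and 8% at 50%. With 1.65 per SD, about 34–40% and 62–64% failed (the ranges span two separate runs of the simulation). The covariate strengths are assumptions; the article gives none.

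**The case against.** On deaths by cause, the strongest defence is that this is a slip in a name. The sentence speaks of competing risks and of cumulative incidence, which fits Aalen–Johansen at least as well as a cumulative hazard, and in that case nothing is overstated. The statistical analysis plan, which is not at hand, may name the right procedure. A comparison of cause-specific cumulative hazards between arms is also valid in itself; only the absolute level under a probability label would be wrong. And the analysis is declared hypothesis generating. All of this stands. It limits the consequence, but the published sentence can still be carried out in two ways.

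On the fallback, the odds ratio is prespecified, reported under its own name and used only on nonconvergence, which is unlikely for the main model. A correctly labelled odds ratio is a different measure, not a wrong one. Counts by arm and Kaplan–Meier curves keep the absolute risks visible. This stands too. What remains is that the planned measure is given up where it could be kept at no cost.

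A reader might infer that the trial will publish inflated deaths by cause and exaggerated treatment effects. The article does not support that. The first would need the literal estimator and a probability reading together; the second would need both nonconvergence and a reader who mistakes an odds ratio for a relative risk. Nor can it be shown that the four DANOHCA reports would end on different scales: the other three protocols are not at hand, and in a factorial trial the same patients and deaths enter each mortality analysis.

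**Conclusion.** Two minor corrections are warranted, both in section 2.7.4.

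- The estimator and the quantity named for deaths by cause do not match. Run as named and read as probabilities, the curves would overstate each cause by a factor of about 1.23 to 1.39, assuming 35–50% total mortality and proportional cause-specific hazards. Whether this would happen cannot be told from the article.
- The nonconvergence rule replaces the planned relative risk with a measure that differs clearly from it at this mortality (RR 0.85 against OR 0.79 to 0.74). It is unlikely to take effect in the main model. It could do so in interaction models with continuous covariates, if those are log-binomial.

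The primary outcome and its test depend on neither.

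**What to change.** 1. Name the Aalen–Johansen estimator for cumulative incidence by cause. Gray's test or cause-specific Cox models for the comparison between arms are optional. If cumulative hazards are what is wanted, label them as such and do not call them incidence.
2. Replace the logistic fallback by modified Poisson regression with robust variance, or obtain the relative risk (and, if wanted, the risk difference) by marginal standardisation from the logistic model. The planned relative risk is then reported whether or not the log-binomial model converges.
3. Bring the statistical analysis plan into line with both changes before unblinding. Section 2.12 expects the last inclusion in July 2026 and the end of follow-up in October 2026.

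The cost is a change of wording. Standard software covers all of it, and no data collection, sample size or primary analysis is affected.
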